[**13.** **Tables** 11](#_Toc141888147)

[a. Baseline characteristics 11](#_Toc141888148)

[b. Primary outcome 12](#_Toc141888149)

[c. Safety outcomes 12](#_Toc141888150)

[d. Secondary outcomes 13](#_Toc141888151)

[**14.** **Figures** 14](#_Toc141888152)

[a. Flowchart of participants 14](#_Toc141888153)

[**15.** **References** 14](#_Toc141888154)

1. **List of abbreviations**

- BTA Botulinum toxin A
- CPP Chronic pelvic pain
- EQ-5D Quality of life questionnaire
- HADS Hospital Anxiety and Depression Scale
- MAPle Multiple Array Probe Leiden
- PCS Pain Catastrophizing Scale
- PFDI-20 Pelvic Floor Distress Inventory 20
- PFIQ-7 Pelvic Floor Impact Questionnaire 7
- PGI-I Patient Global Impression of Improvement
- PISQ-IR Pelvic Organ Prolapse/Incontinence Sexual Questionnaire, IUGA-Revised
- RCT Randomized controlled trial
- QoL Quality of Life
- VAS Visual Analogue Scale

1. **Introduction**
   1. Background

Chronic pelvic pain is common, affecting 15% of women aged 18-50^1^. Pelvic floor muscle spasms resulting in chronic pelvic pain may occur as a primary event or secondary to a physical, psychological or pathological factor. First-line treatment consists of pelvic floor physiotherapy. When first-line treatment fails, more invasive interventions can be done. One previously published intervention is injection with botulinum toxin A (BTA) in the pelvic floor muscles. It produces a localized, partial, and reversible chemical denervation of the muscle which results in localized muscle weakness or paralysis. There is some evidence that injection of BTA in the hypertonic pelvic floor muscles decreases pelvic pain in patients with therapy resistant chronic pelvic pain; however this is not investigated in a randomized controlled trial.

- 1. Objective

The primary objective of this randomized, double-blind, placebo controlled trial was to compare the effect of BTA injections vs. placebo injections on pelvic pain in women with chronic pelvic pain.

1. **Endpoints**
   1. Primary endpoints

Decrease of chronic pelvic pain, measured by a decrease in visual analog scale score (VAS score 0-10) with 33% and a patient global impression of improvement score (PGI-I) of 1 or 2 (better or much better) at 26 weeks after injection.

- 1. Secondary endpoints
     1. Subjective outcomes (patient reported outcomes)
- pelvic floor distress inventory (PFDI-20)^2^
- pelvic floor impact questionnaire (PFIQ-7)^2^
- quality of life (EQ-5D)^3^
- painDETECT^4^

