1. Is the occurrence of missing data random, or is there a discernible pattern among these individuals?
2. What is the source of the missing data?
3. Is there any correlation with specific variables?
4. Can we identify a pattern in the missing data?

Based on the answers to these questions, the potential options for the pattern of missing data are as followed: Missing completely at random (MCAR), missing not at random (MNAR), and missing at random (MAR).

In case of additional analyses not performed using mixed models, missing data will be examined and if necessary randomly imputated.

Patients who are lost to follow-up will be censored at the last visit on which all assessments were completed.

- 1. Interim Analyses and Data Monitoring

No interim analyses are planned.

1. **Efficacy analyses**
   1. Timing of final statistical analysis

The statistical analyses of the primary outcome and secondary outcomes (measured 26 weeks after treatment) will be performed after a minimum of 26 weeks have elapsed from the inclusion of the final patient in the study and after data cleaning for these outcomes has been completed.

The statistical analysis of the follow-up study will be performed 26 weeks after inclusion of the final patient and data cleaning for these outcomes has been completed.

- 1. Primary and secondary outcome analysis

The null hypothesis entails that there is no significant difference in decrease of chronic pelvic pain scores 26 weeks after treatment between the intervention group receiving BTA injections and the control group receiving placebo injections among women with chronic pelvic pain.

VAS score Analysis:

- Mixed models for repeated measurements will be used. VAS scores will be compared over time between groups
- Primary endpoint: Percentage difference in VAS score between baseline and 26 weeks post-treatment will be calculated for each group.

PGI-I Analysis:

- Mixed models for repeated measurements will be used.
- PGI-I scores will be analyzed to identify differences between groups over time.
- Primary endpoint: the primary outcome of PGI-I scores being 1 or 2 (presented as median and interquartile (IQ) range) will be compared between groups.

Secondary outcome analysis

Questionnaire Scores:

- The total scores of all questionnaires will be analyzed over time using mixed models for repeated measurements.
- Analysis will involve assessing changes over time between groups MAPLe

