- EMG signals will be analysed using mixed models for repeated measurements

The analyses will be performed with IBM SPSS Statistics (version 29, Armonk, New York, United States) and R.

In our version 5 statistical analysis, we found that adjusting for baseline and age did not enhance our analysis, given our study's design as a double-blind randomized controlled trial. Therefore, we removed this adjustment from our statistical analysis plan.

1. **Safety analyses**
   1. Adverse events

Adverse event data will be analysed as allocated (intention-to-treat) and 95% confidence interval will be calculated where possible. We do however not foresee a high number of adverse events and in that case adverse events will be mentioned in a table or the text.

- 1. Deaths, Serious Adverse Events and other significant Adverse events

Death/serious adverse events will be described by treatment group.

1. **Other analyses**

Subgroup analysis mentioned in section 6 is seen as hypothesis generating.

1. **Comparison to study protocol**

The current analysis plan is largely based on the published study protocol^11^. Slight changes were made and these are listed below:

- Not only IBM SPSS Statistics for Windows, Version 26.0. will be used, but also R.
- We will not use Kaplan Meier to estimate the success rates at 26 weeks of follow-up. Instead we will use the mixed models for repeated measurements.

1. **Presentation of study results**
   1. Recruitment

The flow of recruitment of study participants will be presented in the CONSORT flow diagram^12^.

- 1. Protocol violations

All protocol violations will be line-listed by treatment group.

- 1. Baseline characteristics

Baseline characteristics of the total randomized (intention-to-treat) population will be presented following the format of the mock table provided in section 13. Discrete outcomes will be presented using absolute numbers and percentages, while continuous outcomes will be presented as means with standard deviations or medians with interquartile ranges.

- 1. Primary outcome

The primary outcome will be presented for the total population as randomised (intention-to-treat). Data will be presented using absolute numbers with percentages for discrete outcomes. Relative Risk or mean difference will be presented together with 95% confidence interval, and p-value otherwise as appropriate.

- 1. Secondary outcomes

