The secondary outcomes will be presented for the total population as randomised (intention-to-treat). Data will be presented using absolute numbers with percentages for discrete outcomes. Relative Risk or mean difference will be presented together with 95% confidence interval, and p-value otherwise as appropriate.

1. **Definition of variables**
   1. Primary outcome

- VAS sore: we will use the painDETECT questionnaire to determine patients VAS score at every time point. We will use the following question out of the painDETECT questionnaire:
  - - - How strong was the pain during the past 4 weeks on average?

We believe that the average pain score over the past 4 weeks provides a more accurate reflection of the current situation than the pain score at the specific moment itself. The latter is influenced by various other factors.

- PGI-I: we will measure our patients interpretation of symptom changes following treatment. A score of 1 or 2 will be considered clinically significant and relevant.
  1. Secondary outcomes
     1. Patient reported outcomes based on questionnaires. Scores of the questionnaires will be calculated in line with the questionnaire instruction.
- pelvic floor distress inventory (PFDI-20): raw outcomes will be transformed into the following results: Pelvic Organ Prolapse Distress Inventory-6 (POPDI-6), Colorectal-Anal distress Inventory 8 (CRAB-8), Urinary distress Inventory 6 (UDI-6) and the PFDI total score
- pelvic floor impact questionnaire (PFIQ-7): raw outcomes will be transformed into the following results: Urinary impact questionnaire (UIQ-7), Colorectal-anal impact questionnaire CRAIQ-7, Pelvic organ prolaps impact questionnaire (POPIQ-7) and the PFQI-7 total score.
- quality of life (EQ-5D)
- painDETECT: raw outcomes will be transformed into a painDETECT total score and will be categorized into negative, unclear and positive.
- pain catastrophizing scale (PCS): raw outcomes will be transformed into a pain catastrophizing total score
- hospital anxiety and depression scale (HADS): raw outcomes will be transformed into: depression score and anxiety score
- the Pelvic Organ Prolapse/Incontinence Sexual Questionnaire, IUGA-Revised (PISQ-IR): raw outcomes will be transformed into the following results:

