**Table 3. Primary outcomes.**

| Outcomes | BTA | Placebo | p-value |
| --- | --- | --- | --- |
| **Pain score** | N=xx | N=xx |  |
| Baseline | Mean (95% CI) | Mean (95% CI) |  |
| 4 weeks follow-up  8 weeks follow-up  12 weeks follow-up  26 weeks follow-up  BTA vs placebo*  Primary endpoint: 33% reduction in pain score, No. (%) | Mean (95% CI) Mean (95% CI) Mean (95% CI) Mean (95% CI)  NNN% | Mean (95% CI)  Mean (95% CI)  Mean (95% CI)  Mean (95% CI)  NNN% | X  X |
| **PGI-I** | N=xx | N=xx |  |
| 4 weeks follow-up  8 weeks follow-up  12 weeks follow-up  26 weeks follow-up  BTA vs placebo*  Primary endpoint: PGI-I 1 or 2, No. (%) | Mean (95% CI)  Mean (95% CI)  Mean (95% CI)  Mean (95% CI)  NNN% | Mean (95% CI)  Mean (95% CI)  Mean (95% CI)  Mean (95% CI)  NNN% | X  X |
| Data are presented as mean [95% CI] unless stated otherwise  *Pain score: average pain score last 4 weeks, scale 0-10.  **Based on linear mixed models including all time points except for baseline. Controlling for pain score (average past 4 weeks) at baseline and age at baseline.  *** p value for interaction | | | |

- 1. Secondary outcomes

| Outcome | Baseline n=xx | 26 weeks  n=xx | p-value |
| --- | --- | --- | --- |
| **PainDETECT total score** ^a^ |  |  |  |
| BTA  Placebo  *Botox vs. placebo | Mean (95% CI)  Mean (95% CI) | Mean (95% CI)  Mean (95% CI) | X |
| **Current VAS score^b^** |  |  |  |
| BTA  Placebo  *Botox vs. placebo | Mean (95% CI)  Mean (95% CI) | Mean (95% CI)  Mean (95% CI) |  |
| **EQ5D VAS score^c^** |  |  |  |
| BTA  Placebo  *Botox vs. placebo | Mean (95% CI)  Mean (95% CI) | Mean (95% CI)  Mean (95% CI) | X |
| **HADS depression scale^d^** |  |  |  |
| BTA  Placebo  *Botox vs. placebo | Mean (95% CI)  Mean (95% CI) | Mean (95% CI)  Mean (95% CI) | X |
| **HADS anxiety scale^d^** |  |  |  |
| BTA  Placebo  *Botox vs. placebo | Mean (95% CI)  Mean (95% CI) | Mean (95% CI)  Mean (95% CI) | X |
| **Pain catastrophizing scale (PCS)^e^** |  |  |  |
| BTA  Placebo  *Botox vs. placebo | Mean (95% CI)  Mean (95% CI) | Mean (95% CI)  Mean (95% CI) | X |
| **PFIQ-7 total score^f^** |  |  |  |
| BTA  Placebo  *Botox vs. placebo | Mean (95% CI)  Mean (95% CI) | Mean (95% CI)  Mean (95% CI) | X |
| **PFDI-20 total score^g^** |  |  |  |
| BTA  Placebo  *Botox vs. placebo | Mean (95% CI)  Mean (95% CI) | Mean (95% CI)  Mean (95% CI) | X |
| **PISQ-IR total score^h^** |  |  |  |

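### The yes/no PGI-I component of the primary endpoint is given a median and interquartile range in one section and a number and percentage in others, and no binary analysis is named for it

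*SAP*

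**What the plan says.** Endpoints (Primary endpoints) makes PGI-I one of two components of the primary endpoint: "a patient global impression of improvement score (PGI-I) of 1 or 2 (better or much better) at 26 weeks after injection". Definition of variables confirms the cut-off: "A score of 1 or 2 will be considered clinically significant and relevant".

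Efficacy analyses (Primary and secondary outcome analysis, under PGI-I) names mixed models for repeated measurements and says that "PGI-I scores will be analyzed to identify differences between groups over time". Its primary-endpoint bullet then states that "the primary outcome of PGI-I scores being 1 or 2 (presented as median and interquartile (IQ) range) will be compared between groups".

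Three other places bear on the same component:

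- Table 3 gives the PGI-I rating at each visit as a mean with a 95% interval. A separate row, which begins "Primary endpoint: PGI-I 1 or 2, No", calls for number and percentage per arm. A footnote reads "Based on linear mixed models including all time points except for baseline".
- Presentation of study results (Primary outcome) says "Data will be presented using absolute numbers with percentages for discrete outcomes". It adds a relative risk or a mean difference with a 95% interval.
- Comparison to study protocol says "We will not use Kaplan Meier to estimate the success rates at 26 weeks of follow-up" and puts the mixed models in its place.

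**The concern.** A woman either has a rating of 1 or 2 at week 26 or she does not. The natural summary is a proportion, and the natural effect measure is a risk difference or relative risk. A median and interquartile range describe neither.

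The model has the same problem. A mixed model of ratings estimates a difference in mean rating. That is a different hypothesis from more women reaching 1 or 2, and it yields neither a success rate nor the relative risk that the presentation section promises. Yet the comparison with the protocol says that mixed models take over from Kaplan-Meier for exactly those success rates.

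At stake is one component of the primary endpoint, however it is combined with the VAS component. The analyst must choose which section to follow for the summary, and must choose a test that no section names. Both choices could be made after the data are seen.

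**Working it through.** **Inputs.** From the SAP: 94 women in total, so 94 / 2 = 47 per arm; success is a rating of 1 or 2. The SAP gives no expected PGI-I success rates, so there is no figure of its own to reproduce on this point. (The 94 is derived for pain scores and is not in dispute here.) All counts below are assumed for illustration.

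**Step 1: median and interquartile range of the yes/no outcome.** Code success as 1 and sort the 47 values.

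- The median is the 24th value, so it is 0 whenever there are at most 23 successes.
- The upper quartile is the 36th value, or the midpoint of the 35th and 36th, depending on the definition. Under both it is 1 once there are at least 13 successes.
- The lower quartile is 0 throughout this range.

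Every count from 13 (13/47 = 27.7%) to 23 (23/47 = 48.9%) therefore prints as 0 (0 to 1).

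**Step 2: median, interquartile range and mean of the ratings.** Perhaps the bullet means the ratings themselves. Take these two arms:

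| Rating | 2 | 3 | 4 | 5 | Total |
|---|---|---|---|---|---|
| Arm A | 13 | 21 | 13 | 0 | 47 |
| Arm B | 23 | 5 | 15 | 4 | 47 |

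- Mean A = (26 + 63 + 52) / 47 = 141 / 47 = 3.00.
- Mean B = (46 + 15 + 60 + 20) / 47 = 141 / 47 = 3.00.
- In both arms the median is 3 and the interquartile range is 2 to 4, under both quartile definitions.
- A two-sample t-test, standing in for the week-26 contrast of a linear model with complete data, compares 3.00 with 3.00 and gives p = 1.00.

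**Step 3: the endpoint in the same two arms.**

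- Success is 13/47 = 27.7% against 23/47 = 48.9%.
- Risk difference = 10/47 = 21.3 points. Standard error = √(0.277 × 0.723 / 47 + 0.489 × 0.511 / 47) = 0.098, so the 95% interval is 2.1 to 40.5 points.
- Relative risk = 23/13 = 1.77. Standard error of its log = √(1/23 − 1/47 + 1/13 − 1/47) = 0.279, so the 95% interval is 1.02 to 3.06.
- Chi-square without correction gives p = 0.034; Fisher's exact test gives p = 0.055.

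Median, range and mean rating all agree between the arms while the success proportions differ by 21.3 points. The last line shows a second cost: with no test named, the choice between two ordinary ones puts this example on either side of 0.05.

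**Step 4: missing ratings.** Missing data (under Analysis considerations) relies on the mixed model, and leaves any analysis outside it to random imputation if that is thought necessary. Because the binary analysis is unnamed, the handling of a missing week-26 PGI-I in the number, percentage and relative risk is also open.

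**The case against.** A reader might infer that the SAP never yields a success proportion, so that clearly different arms would look identical in the report. The document does not support that. The Table 3 row would print 13 (27.7%) and 23 (48.9%), and the presentation section asks for percentages and allows a relative risk with its interval. This answers the stronger reading fully.

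A reader might also see several incompatible summaries of one variable. That is too strong. A mean rating per visit and a responder percentage are two quantities that can stand together in one table. Only the median and range attached to the responder outcome is out of place.

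The description of the model as linear is also weaker than it looks. Neither Efficacy analyses nor Comparison to study protocol uses that word; for PGI-I it comes from the Table 3 footnote. That footnote still adjusts for baseline pain and age, which Efficacy analyses says was removed, and its marker does not match the one in the table body. The general term mixed models could cover a binary mixed model. Table 3 may also intend a separate p-value for the responder row, but the extracted layout does not settle this.

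What stands is narrower. Efficacy analyses speaks of modelling scores and specifies no binary form. The other sections say how to display the component, but not which model or test produces its relative risk, interval and p-value.

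**Conclusion.** The concern holds as an internal contradiction plus an unnamed analysis. The median and interquartile range in Efficacy analyses is the wrong summary for a yes/no component, and it conflicts with Table 3 and with Presentation of study results. The only method described for PGI-I is a model of scores. If that is a model of mean ratings, as the Table 3 footnote indicates, it does not estimate the success rates that Comparison to study protocol assigns to mixed models.

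The example shows that a 21.3-point difference in success can coexist with equal medians, ranges and means. It shows what is possible, not what is likely: the counts are assumed, and the t-test only approximates a model that uses all visits. Because the proportions would still be reported, this should be fixed but does not leave the component unreported.

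**What to change.** 1. In Efficacy analyses, delete the median and interquartile range for this component. State instead that PGI-I 1 or 2 at week 26 is reported as number and percentage per arm, with a risk difference and/or relative risk, 95% interval and p-value from one pre-named binary-outcome model. Modified Poisson regression would serve, as would a binary repeated-measures model with the week-26 contrast.
2. State how a missing week-26 PGI-I enters the numerator, the denominator and that model.
3. Keep the mixed model of PGI-I ratings over time as a supportive analysis. A proportional-odds mixed model is an option, not a requirement.
4. In Comparison to study protocol, say that the model estimating success rates is the binary one, and make the Table 3 footnote show which model belongs to which row.

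The cost is a few sentences in the SAP and one extra analysis in R, which the SAP already lists. No new data are needed.

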**Table 3. Primary outcomes.**

| Outcomes | BTA | Placebo | p-value |
| --- | --- | --- | --- |
| **Pain score** | N=xx | N=xx |  |
| Baseline | Mean (95% CI) | Mean (95% CI) |  |
| 4 weeks follow-up  8 weeks follow-up  12 weeks follow-up  26 weeks follow-up  BTA vs placebo*  Primary endpoint: 33% reduction in pain score, No. (%) | Mean (95% CI) Mean (95% CI) Mean (95% CI) Mean (95% CI)  NNN% | Mean (95% CI)  Mean (95% CI)  Mean (95% CI)  Mean (95% CI)  NNN% | X  X |
| **PGI-I** | N=xx | N=xx |  |
| 4 weeks follow-up  8 weeks follow-up  12 weeks follow-up  26 weeks follow-up  BTA vs placebo*  Primary endpoint: PGI-I 1 or 2, No. (%) | Mean (95% CI)  Mean (95% CI)  Mean (95% CI)  Mean (95% CI)  NNN% | Mean (95% CI)  Mean (95% CI)  Mean (95% CI)  Mean (95% CI)  NNN% | X  X |
| Data are presented as mean [95% CI] unless stated otherwise  *Pain score: average pain score last 4 weeks, scale 0-10.  **Based on linear mixed models including all time points except for baseline. Controlling for pain score (average past 4 weeks) at baseline and age at baseline.  *** p value for interaction | | | |

- 1. Secondary outcomes

| Outcome | Baseline n=xx | 26 weeks  n=xx | p-value |
| --- | --- | --- | --- |
| **PainDETECT total score** ^a^ |  |  |  |
| BTA  Placebo  *Botox vs. placebo | Mean (95% CI)  Mean (95% CI) | Mean (95% CI)  Mean (95% CI) | X |
| **Current VAS score^b^** |  |  |  |
| BTA  Placebo  *Botox vs. placebo | Mean (95% CI)  Mean (95% CI) | Mean (95% CI)  Mean (95% CI) |  |
| **EQ5D VAS score^c^** |  |  |  |
| BTA  Placebo  *Botox vs. placebo | Mean (95% CI)  Mean (95% CI) | Mean (95% CI)  Mean (95% CI) | X |
| **HADS depression scale^d^** |  |  |  |
| BTA  Placebo  *Botox vs. placebo | Mean (95% CI)  Mean (95% CI) | Mean (95% CI)  Mean (95% CI) | X |
| **HADS anxiety scale^d^** |  |  |  |
| BTA  Placebo  *Botox vs. placebo | Mean (95% CI)  Mean (95% CI) | Mean (95% CI)  Mean (95% CI) | X |
| **Pain catastrophizing scale (PCS)^e^** |  |  |  |
| BTA  Placebo  *Botox vs. placebo | Mean (95% CI)  Mean (95% CI) | Mean (95% CI)  Mean (95% CI) | X |
| **PFIQ-7 total score^f^** |  |  |  |
| BTA  Placebo  *Botox vs. placebo | Mean (95% CI)  Mean (95% CI) | Mean (95% CI)  Mean (95% CI) | X |
| **PFDI-20 total score^g^** |  |  |  |
| BTA  Placebo  *Botox vs. placebo | Mean (95% CI)  Mean (95% CI) | Mean (95% CI)  Mean (95% CI) | X |
| **PISQ-IR total score^h^** |  |  |  |
| BTA  Placebo  *Botox vs. placebo | Mean (95% CI)  Mean (95% CI) | Mean (95% CI)  Mean (95% CI) | X |
| **Pelvic Floor Resting Tone^i^** |  |  |  |
| BTA  Placebo  *Botox vs. placebo | Mean (95% CI)  Mean (95% CI) | Mean (95% CI)  Mean (95% CI) | X |

Data presented as mean (95% confidence interval) or p-value.

* Based on linear mixed models. Controlling for average pain and age at baseline.

^a^ A lower score indicates nociceptive pain (<12) and a higher score indicates neuropathic pain (>19). In between (13-18) there is possible neuropathic pain.

^b^ Visual analog scale score (0-10) at time of questionnaire.

^c^ EQ VAS component: records the patients self-rated health on a vertical visual analog scale (0-100), higher score indicates a better self-rated health

^d^ Hospital anxiety and depression scale, categorized in normal (0-7), borderline normal (8-10) and abnormal (11-21)

^e^ Pain catastrophizing scale, a higher score indicates a greater degrees of pain catastrophizing. A total score of >30 represents a clinically significant level of pain catastrophizing.

^f^ Pelvic floor impact questionnaire, higher score indicate more impact on daily activity

^g^ Pelvic floor distress inventory (scale 0-300), higher score indicate more symptom distress

^h^ Pelvic Organ Prolapse/Incontinence Sexual Questionnaire, IUGA-Revised, a higher score indicates a better sexual function

^I^ Measured by MAPLe

1. **Figures**
   1. Flowchart of participants

[figure not shown]

1. **References**
4. Rabin R, de Charro F. EQ-5D: a measure of health status from the EuroQol Group. Ann Med. 2001 Jul;33(5):337-43. doi: 10.3109/07853890109002087. PMID: 11491192.

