- pain catastrophizing scale (PCS)^5^
- hospital anxiety and depression scale (HADS)^6^
- sexual function (PISQ-IR)^7^
- Visual analog scale (VAS) score ^8^
  - 1. Anatomical outcomes
- Pelvic floor hypertonicity measured by the MAPLe device
  - 1. Other outcomes
- A cost-effectiveness analysis will be performed in case of a significant improved VAS score and quality of life.
  1. One year follow-up

To evaluate the safety and efficacy of a BTA injection one year after BTA injection.

- 1. Open label extension study

To evaluate the safety of BTA injection 26 weeks after the placebo injection in participants who did not reach the primary endpoint.

1. **Study methods**
   1. Study design

Double-blinded randomized placebo-controlled trial.

- 1. Study population

Patients over 16 years with >6 months of chronic pelvic pain with pelvic floor muscle hypertonicity refractory to first-line pelvic floor physiotherapy, and in whom no anatomical cause was found.

* Definition by the International Continence Society: Chronic pelvic pain is characterized by persistent pain lasting longer than 6 months or recurrent episodes of abdominal/pelvic pain, hypersensitivity or discomfort often associated with elimination changes, and sexual dysfunction often in the absence of organic etiology^9^.

- 1. Inclusion criteria
- Female, >16 years
- Chronic pelvic pain according to the ICS with or without dyspareunia
- Vaginal examination with one finger possible
- Pelvic floor hypertonicity measured by physical examination by registered pelvic floor physiotherapist and MAPLe
- Previous physical therapy with registered physical therapist was unsuccessful
- Good understanding of Dutch language
- Willing to provide informed consent
  1. Exclusion criteria
- (wish for) Pregnancy/lactation during study period
- Previous pelvic floor BTA treatment
- Known hypersensitivity to BTA
- History of neuromuscular or bleeding disorders
  1. Treatment of subjects

The pelvic floor muscles will be injected with either 100 IU BTA or placebo.

- 1. Study procedures

The subjects will undergo the following procedures after signing informed consent:

- Physical examination by a gynecologist and a physical therapist
- MAPLe measurement by a physical therapist
- The patient preference questionnaire will be filled in
- The validated questionnaires will be filled in at baseline, 4, 8, 12 and 26 weeks after injection
- Injection of study medication or placebo in pelvic floor muscles

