If withdrawal occurs before the injection, these patients will be replaced in order to reach the desired statistical power. If withdrawal occurs during the follow-up period, between injection and before the endpoint of 26 weeks, the data will be censored at the last available time-point. Analyses of available data will be performed in the intention to treat group.

1. **Sample-size**

The ANCOVA procedure^10^ showed that to detect a statistical significant 33% difference in pain scores between the intervention group and the control group, a sample size of 94 individuals was required for this trial (47 per group), with 80% power and assuming a two-sided alpha of 0.05.

1. **Analysis considerations**

To evaluate the effect of BTA on the VAS score during follow-up all statistical analysis will be performed according to intention to treat principle.

- 1. Analysis of groups

The intention-to-treat (ITT) population is the as-randomized population. This will consist of all patients who have given consent and have been allocated to one of the two treatments, irrespective of treatment received.

- 1. Covariates and Subgroups

Subgroup analyses are planned to investigate the possible effect on the outcome of treatment of the following possible pre-defined interaction terms:

- Menopausal status (yes vs. no)
- Negative sexual experience (yes vs. no)
- Depression scale at baseline (HADS) (scale 0-21 points)
- Previous operations (Abdominal/pelvic operation vs other)
- Parity (absolute numbers)
- Use of pain opioids (yes vs. no)
- Sexual activity (yes vs. no)

Subgroup analyses will be conducted by adding an interaction term to the model and testing for the statistical significance of this interaction term. We will subsequently examine the likelihood that we have missed any relevant interaction terms through a likelihood ratio test for all baseline characteristics available.

In version 5 of our statistical analysis plan we added one subgroup to our analysis:

- Duration of CPP (<1 year vs. >1 year)

Furthermore, due to our study design (double-blind randomized controlled trial), we determined that covariates did not add value to our analysis.

- 1. Missing data

We will use mixed models for repeated measurements and its ability to handle missing data effectively. Before analyzing our results using mixed models for repeated measurements, the following questions will be answered:

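### The SAP gives conflicting covariate models for the secondary outcomes, and neither conditions a contrast on that outcome's own collected baseline

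*SAP*

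**What the plan says.** Three parts of the SAP describe the secondary model.

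- **Section 13, secondary-outcomes table, footnote.** The between-arm row of every outcome is "Based on linear mixed models. Controlling for average pain and age at baseline". The footnote does not say whether the baseline value is among the modelled responses.
- **Section 7, Primary and secondary outcome analysis.** "The total scores of all questionnaires will be analyzed over time using mixed models for repeated measurements", and "Analysis will involve assessing changes over time between groups". No covariate is named. The section closes by saying that, for version 5, "we found that adjusting for baseline and age did not enhance our analysis", and "Therefore, we removed this adjustment from our statistical analysis plan".
- **Section 6, Covariates and Subgroups.** Citing the double-blind randomised design, "we determined that covariates did not add value to our analysis".

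On data collection, Section 4 (Study procedures) states: "The validated questionnaires will be filled in at baseline, 4, 8, 12 and 26 weeks after injection". The secondary-outcomes table has a baseline column for every outcome, including MAPLe resting tone.

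For comparison, the primary-outcome table is explicit about the response: "Based on linear mixed models including all time points except for baseline". It then controls for baseline average pain, which for the pain score is its own baseline.

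**The concern.** Two things are wrong. First, the footnote and the body text cannot both hold: one adjusts for average pain and age, the other for nothing. Second, settling that conflict either way does not give a good model. For HADS, PCS, PFDI-20, PFIQ-7, PISQ-IR, EQ VAS and resting tone, average pain is the baseline of a different variable. The outcome's own baseline is usually its best single predictor, and under neither text is it conditioned on.

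The design argument in Sections 6 and 7 does not answer this. Randomisation removes baseline differences in expectation. It does not remove the chance difference in one trial of 47 per arm, nor the outcome variance that a measured baseline would explain.

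At stake is the width of the secondary intervals. These outcomes include the only anatomical endpoint (resting tone), and quality of life, which is one of the two conditions in Section 3 for the cost-effectiveness analysis.

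**Working it through.** **The plan's own figure.** Section 5 gives 94 women (47 per group), 80% power, two-sided alpha 0.05, by an ANCOVA procedure for pain scores. It cannot be reproduced, because no SD, baseline mean or correlation is stated. Only 47 per arm is used below.

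**Assumed inputs (none is in the SAP).**
- r: correlation of an outcome's week-26 value with its own baseline; 0.3, 0.5, 0.7.
- q: correlation of baseline average pain with the week-26 outcome; 0.2, then varied.
- Outcome variance set to 1 and equal at both times. Age, the intermediate visits and the degree of freedom spent on a covariate are ignored.

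**Residual variance of the week-26 contrast under each reading.**
- No covariate, follow-up values only: 1
- Pain only: 1 − q² = 1 − 0.04 = 0.96
- Baseline as an unconstrained response (in effect a change score): 2(1 − r)
- Own baseline as covariate: 1 − r²

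| r | own baseline | change score | own vs pain-only | own vs none | own vs change score |
|---|---|---|---|---|---|
| 0.3 | 0.91 | 1.40 | √(0.91/0.96) = 0.97 | √0.91 = 0.95 | √(0.91/1.40) = 0.81 |
| 0.5 | 0.75 | 1.00 | √(0.75/0.96) = 0.88 | √0.75 = 0.87 | √(0.75/1.00) = 0.87 |
| 0.7 | 0.51 | 0.60 | √(0.51/0.96) = 0.73 | √0.51 = 0.71 | √(0.51/0.60) = 0.92 |

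The last three columns are ratios of interval width. The intervals are therefore narrower by about 3% / 12% / 27% (against pain-only), 5% / 13% / 29% (against none) and 19% / 13% / 8% (against a change score).

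**Sensitivity to q.** At r = 0.5, the narrowing against pain-only is 12% at q = 0.2, √(0.75/0.91) = 0.91 or 9% at q = 0.3, and √(0.75/0.84) = 0.94 or about 6% at q = 0.4. It vanishes where pain predicts the outcome as well as the outcome's own baseline does (q = r).

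**Chance imbalance.** The standard error of a baseline difference D between arms is √(2/47) = 0.206 SD. A follow-up-only contrast retains rD. An unconstrained change contrast subtracts all of D and so overshoots by (1 − r)D. At r = 0.5 each is 0.5 × 0.206 = 0.10 SD for a one-standard-error imbalance. Pain adjustment removes only the part of D that pain shares.

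**In terms of power, for illustration.** An effect of 0.584 SD has 80% power unadjusted at 47 per arm (two-sample t-test). It has 81.6% with pain-only adjustment at q = 0.2, and 83.6% / 89.9% / 97.5% with own baseline at r = 0.3 / 0.5 / 0.7. The SAP sets no power target for secondary outcomes, so this only restates the interval widths.

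**The case against.** The strongest reply is that the footnote is probably left over from before version 5, so the conflict is editorial and the operative model is the unadjusted one. A reader might infer that average pain is the settled covariate for the secondary outcomes; Sections 6 and 7 do not support that. The conflict still has to be resolved, and the unadjusted model does not use own baseline as a covariate either.

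A second reply is that baseline may already be in the model. Section 7 speaks of changes over time, and the secondary footnote, unlike the primary one, does not exclude baseline from the response. This stands in part. One cannot say without condition that chance baseline differences pass forward into the contrast: that holds if only follow-up values are modelled. If baseline is an unconstrained response, the difference is subtracted, at the cost of the change-score variance.

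Three stronger inferences are not supported:
- **Bias or a wrong type I error rate.** Under 1:1 randomisation each of these contrasts is valid; the loss is efficiency and conditional imbalance.
- **A quality-of-life result that alone triggers the cost-effectiveness analysis.** Section 3 requires improved VAS and quality of life jointly.
- **An effect on the sample size of 94.** Section 5 concerns pain scores, not the secondary outcomes.

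It is also fair that every correlation is assumed, that the gain over pain-only adjustment is small at r = 0.3, and that average pain may be a close proxy for current VAS.

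**Conclusion.** The point holds as a contradiction plus an avoidable loss of precision. The footnote and the body text give different secondary models, and neither conditions on the outcome's own baseline although it is collected. Under the assumed correlations the week-26 interval could be from about 3% to 29% narrower, depending on r and on which reading of the SAP applies. The comparison with pain-only adjustment matters only if the footnote governs, and shrinks as pain's own correlation with the outcome rises. The actual size cannot be fixed from the SAP. The change is worth making because it uses data already collected and settles an ambiguity that must be settled anyway.

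**What to change.** Amend these places together, so that no new conflict arises: the footnote to the secondary-outcomes table in Section 13, the secondary-outcome text in Section 7, the Section 7 closing paragraph on removal of adjustment, and the Section 6 statement on covariates.

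Suggested model: for each secondary outcome, a mixed model of its post-injection values (questionnaires at 4, 8, 12 and 26 weeks; MAPLe at its post-injection measurements) with treatment, visit, treatment-by-visit, that outcome's own baseline and baseline-by-visit. The reported result is the adjusted week-26 difference with 95% CI. Alternatively, keep baseline as a response and constrain the arm means to be equal there. If average pain and age are to remain as additional covariates, all of these places should say so.

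The cost is SAP wording and one covariate with its visit interaction per model; no new data are needed. In the covariate version, women without a baseline value drop out; the constrained-baseline version avoids this.
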